### Qualitative semistructured interviews with subsamples of people living with dementia and carers/staff

#### Data collection

In-depth semistructured interviews will be conducted with a (1) subsample of participants living with dementia (n=35) and (2) their (informal or formal) carers (n=35) across the same time frame as the quantitative data collection, during an additional visit to the participant. The selection is based on the availability of a dyad (person living with dementia and a carer) to examine convergence/divergence in beliefs over the course of the study. Interview topic guides will explore:
The participants' previous engagement with art, using cultural capital^ii^ as a theoretical framework to guide the analysis. This explores attitudes towards art, what people define as ‘art’, engagement with ‘art’ in galleries or everyday art. This will enable changes in arts engagement to be understood. The construct of social capital^iii^ is used to aid the analysis of connectivity, as it provides a systematic way of thinking about the qualities of communities (baseline).The boundary and nature of the community as experienced by the people with dementia themselves, exploring how community boundaries are perceived, the extent to which opportunities exist to interact with others within the community boundary and how this changes over the time of the intervention (baseline).The changes in the above themes (a and b) and the extent to which changes (if any) have been sustained and/or lead to new aspects of social connectivity (T2 and T3).

#### Analysis

Qualitative data will be digitally recorded and professionally transcribed for analysis. Software such as QSR NVivo will be used to aid analysis. Thematic analysis^37^ is used to identify themes that originate from the data (inductive) and the analysis may also be guided by the theory (deductive), such as community and in terms of responses to art, cultural and social capital. Detailed readings of the interview transcripts will help establish a familiarity with the data and encapsulate the emerging themes. An outline coding scheme to highlight meaning will be developed.^43^ The range and variation of themes may be explored using data displays.^44^

### Health economics

The health economics component conducts a social return on investment (SROI) evaluation of the intervention. This involves six stages:^45^ establishing the scope and identifying key stakeholders; mapping outcomes; evidencing outcomes and giving them a value; establishing impact; calculating SROI; reporting, using and embedding. The principles are: stakeholder involvement; understanding changes; valuing things that matter; including only what is material; avoidance of overclaiming; transparency; verification of results. A small number (up to 15) separate interviews will be held with stakeholders directly involved in the study and with those who work in the area but are not directly involved in the study. Questions included in the main interviews focus on the need to establish value ‘contingent valuation’ (which can be monetarised) and in determining impact.

#### Analysis

The evaluative SROI will be conducted in accordance with the principles and methodology set out in the Cabinet Office guide.^45^ This involves (1) mapping outcomes, constructing an impact map informed by the engagement with stakeholders. The range of costs and benefits to be measured will be identified; (2) evidencing outcomes and giving them a value; (3) establishing impact, considering deadweight and displacement (what would have happened without the intervention), attribution (how much of the outcome should be assigned to the activities of other organisations), drop-off (how long the outcomes lasted); (4) calculating the SROI, using the data assimilated in the earlier stages to calculate the SROI and conduct appropriate sensitivity analysis; (5) reporting, using and embedding.

### Public engagement

Public engagement projects using the work from Dementia and Imagination are under development. These will be highly interactive with a national, strategic focus and regional activity. An example of the activities is given below in table 2.

**Table 2 BMJOPEN2016011634TB2:** Example of public engagement activities

Activity/project title	Engagement questions	Outcomes/output	Target of activity	Data
Practising imagination through visual art	How can I have fun with my clients/spouse/partner? How can I learn more about helping someone living with dementia? How can I learn what a person with dementia is capable of? What are the best ways of using visual arts to enrich the lives of those with dementia?	Each of the 3 sites to run practitioner workshops/training sessions, using ‘A Practitioners Guide to Dementia and Imagination’ and online resources	More people delivering arts activities as part of care for people living with dementia Developing skills for those working in the care of people living with dementia, including family carers	Short evaluations; longer term follow-up to ascertain practice changes

### Artistic practices

Most interventions using artistic and cultural methods are assessed primarily with regard to their impact on participant individuals or communities. There has been much less interest in the specific cultural or aesthetic element of interventions or the impact on the aesthetic or artistic practitioners themselves. This is developed in three ways, using longitudinal group interviews with three artists employed to respond, aesthetically, to the research programme; using focus groups with the artistic practitioners delivering the interventions; and exploring participatory and coproduced methods over the course of the project. These approaches aim to answer the core question(s) of how the practitioners' understandings of dementia change in response to the project, how the practice itself is affected (including, eg, the use of new or mixed aesthetic methods), and the practitioners relationship to research. These three questions contribute to the gap in evaluation literature that has, to date, not fully engaged with the aesthetic practice aspects of aesthetic interventions.

### Data integration across the work programme

Results from the quantitative and qualitative data for all work packages will be integrated as much as possible. There are various ways of combining the results from qualitative and quantitative data sets, in addition to corroboration, which will inform the synthesis of our data.^46^ These include elaboration, where one type of data adds to the understanding being gained by another type of data; complementarity, where analysis of qualitative and quantitative data sets generate complementary insights that improve overall understanding of a particular topic; and contradiction, where qualitative and quantitative findings conflict and give rise to juxtapose positions to be explored in further research. The synthesis of quantitative and qualitative data will ensure that the findings are as comprehensive as possible and provide a sound basis for generating research, policy and practice recommendations. Data integration will enable further theoretical development in visual art and dementia research. The longitudinal element of the concurrent data collection provides an opportunity to examine the temporal aspects.

### Ethics and dissemination

All participant information provided is prepared in an acceptable manner that is clear and understandable. Bilingual information (Welsh and English) is prepared in Wales. All research staff and artists who will have direct contact with participants will undertake a programme of training developed by the research team. This will cover the MCA, informed consent, dementia awareness and the study protocol procedures, including data collection methods and data management. Professional standards as set out in the Research Councils UK (RCUK) Policy and Guidelines on Governance of Good Research Conduct are adopted by the study.

A requirement of UK research councils is that data resulting from the study are shared with the wider research community through the UK Data Archive. Data management protocols will be followed to ensure confidentiality and anonymity and protection of personal data. All data will be anonymised and stored separately from any identifying details. For contact purposes, these are linked through a unique identifier. Hard copy data will be stored securely in locked filing cabinets and electronically in password-protected folders. Access will only be available to the research team. The lead investigator will coordinate the sharing of data within the research team. Any transmission of data/transcripts will be through a secure method and encrypted. In terms of digital data (film/photography/audio) all qualitative interviews will be recorded using digital recording devices and securely stored as audio files (mp3) and encrypted.

Two types of visual data will be obtained. One is through videoing the observation sessions, and is purely for research purposes only. This will be securely stored through networked security. The other is artistic output, which will be handled sensitively, with the wishes of the participant being observed at all times. This will be securely stored and its use managed through the research team. Copyright will be held with specific investigators in the research team at each of the three data collection sites (as they are the employers).

The research findings will be shared through a range of activities. International and national academic conferences and events will be attended to present papers and lead symposia. The project has developed an extensive public engagement and communication strategy to maximise the planned pathways to impact. This takes into account the variation in needs, concerns and preferred ways of working and communicating of each significant beneficiary group. Public engagement projects will target a broad range of stakeholders. A project website will be developed as a resource bank for stakeholders and a continuing legacy from the project. A quarterly newsletter will be produced. Policy and practice summaries will be developed from the findings. The current visual arts intervention protocol will be developed as a practitioners guide, freely available as an electronic resource as well as a hard copy version.

## Discussion

Dementia and Imagination is the largest arts and dementia research study in the UK. It seeks to address not only health-related issues, but broader societal factors that impact on the lives of people living dementia, notably the right to social inclusion, good quality care and supportive communities. Drawings on a range of scientific areas are highlighted as an important contribution to future dementia research.^47^ The combination of arts and science in this research enables the generation of a broad range of data for an in-depth synthesis. Despite the strengths of the study, some limitations should be recognised at the outset. A major challenge for dementia research is measuring the impact of psychosocial interventions. A number of standardised and validated measures exist, some we incorporate into our protocol. However, the extent the measures are sensitive enough to capture change in relation to a complex intervention such as a visual arts intervention are unclear. In recognising these challenges at the outset, the mixed-methods approach will enable qualitative exploration which may reveal more subtle impact and experiences to be identified.

The economic analysis adopts a SROI, which uses a broader stakeholder perspective than a cost-utility analysis, but it is open to some criticism.^48^
^49^ One of the key criticisms is that while SROI evaluations typically report detailed information on sources of information and financial proxies, the arbitrary nature of selecting financial proxies is an area for concern as much depends on the assumptions made by the researchers. To minimise the risk of overclaiming benefits, SROI analyses incorporate deadweight, attribution and drop-off rates. In Dementia and Imagination, we include questions about participants' other activities to obtain more robust estimates of deadweight and attribution, and the drop-off will be calculated by observing differences between baseline and end of study values.

A further limitation is that the study design cannot focus on a more robust test of effectiveness, as a randomised controlled trial was beyond the remit of the available resources. However, with the exception of randomisation, the study assesses a range of processes that would traditionally be the focus of a pilot study (eg, recruitment, retention, eligibility criteria, different forms of data collection with a range of measures, personnel issues, data management, etc) which will usefully serve the next stage in seeking funding for a definitive trial of the intervention.

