##### Data collection (people living with dementia)

The following quantitative and qualitative questionnaire data are collected in a face-to-face interview by the researcher at time 1 (baseline) prior to the start of the intervention, time 2 (follow-up) at the end of the intervention and time 3 (longer term follow-up) 3 months after the time 2 assessment.
Demographic data (eg, age, gender, marital status, socioeconomic status, education, residence).Social connectedness (Lubben Social Network Scale, six items;^31^ emotional and social loneliness, six items).^32^Dementia Quality of Life.^33^ A 28-item measure of QoL designed for people with dementia.Medication use (limited to particular types of psychotropics and those prescribed for dementia).Extent of engagement with art activities (qualitative).Expectations of taking part (qualitative, baseline only).Sense of belonging to community (five items).Memory of the sessions (qualitative, follow-up only).Perceived benefits and value (qualitative, follow-up only).

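### The stated SROI drop-off calculation compares baseline with end of study and omits the end-of-programme value, so it cannot measure how long benefit lasted

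*Protocol article*

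**What the plan says.** Two places in the protocol article deal with drop-off.

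- The Analysis subsection under Health economics lists it among the steps for establishing impact and explains it as "drop-off (how long the outcomes lasted". It gives no calculation.
- The Discussion gives its purpose: "To minimise the risk of overclaiming benefits, SROI analyses incorporate deadweight, attribution and drop-off rates". It then gives the only calculation in the article: "the drop-off will be calculated by observing differences between baseline and end of study values".

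The assessment times are set out under Data collection for people living with dementia. T1 comes before the programme begins and T2 when it finishes; the last assessment is "time 3 (longer term follow-up) 3 months after the time 2 assessment". The staff and carer sample follows the same three-point schedule. The Health economics section also names "avoidance of overclaiming" as one of the principles of the evaluation.

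**The concern.** How long an outcome lasted can be judged only against the level reached when the programme stopped. That level is measured at T2. The calculation in the Discussion names baseline and end of study and leaves T2 out. It therefore describes a different quantity from the one defined in the Health economics section: the benefit still present at the end, rather than the benefit lost since the programme ended.

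Cost–benefit is one of the study's listed objectives, and the SROI is how it is addressed. Drop-off is one of three adjustments offered as protection against overclaiming. In a study without randomisation, a reader will rely on those adjustments when judging the ratio. If drop-off is not identified by its stated calculation, that protection is not secured.

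**Working it through.** The article gives no numerical drop-off rate, so there is no figure to reproduce. The check is algebra on the three assessments, followed by an illustration with assumed scores.

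**Inputs from the article.** T1 is before the intervention, T2 at its end, T3 three months after T2. Drop-off is meant to describe persistence. The stated contrast is baseline against end of study.

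**Formulas**, for an outcome scored so that higher is better:

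- Gain over the programme: G = T2 − T1.
- Loss after the programme as a share of the gain: D = (T2 − T3)/(T2 − T1).
- Stated contrast as a share of the gain, reading end of study as T3: R = (T3 − T1)/(T2 − T1).
- Sum: D + R = (T2 − T1)/(T2 − T1) = 1.

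The stated contrast is thus the retained share, the complement of drop-off. It can be turned into drop-off only if T2 is also known.

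**Illustration.** Assumed T1 = 50 and T2 = 60, so G = 10. The last two columns show the benefit credited after the programme, G × (1 − rate), using D or R as the rate.

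| Case | T3 | D | R | Credited with D | Credited with R |
|---|---|---|---|---|---|
| Fully sustained | 60 | 0% | 100% | 10 | 0 |
| Three quarters kept | 57.5 | 25% | 75% | 7.5 | 2.5 |
| Half kept | 55 | 50% | 50% | 5 | 5 |
| Fully lost | 50 | 100% | 0% | 0 | 10 |
| Below baseline | 47 | 130% | −30% | −3 | 13 |

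D and R agree only when exactly half the gain is lost. The last column applies only if the stated difference is itself taken as the rate deducted.

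**Weaker reading, in which the difference is only observed.** Compare scores of 50, 50, 50 (no benefit at any time) with 50, 60, 50 (a 10-point gain fully lost). In both, T3 − T1 = 0. The first has no benefit to discount; the second has a drop-off of 100%. The stated pair of values cannot tell them apart.

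**Alternative reading, end of study = T2.** The contrast becomes (T2 − T1)/(T2 − T1) = 100% of the gain in every row, whatever happens afterwards. It carries no information on persistence.

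**The case against.** The strongest reply is that the sentence is a brief remark in the Discussion of a condensed article, while the methods section describes drop-off correctly, refers to a published SROI guide and plans to "conduct appropriate sensitivity analysis". T2 is collected, nothing bars its use, and the gain from T1 to T2 is needed to value an outcome at all. The authors may have meant to compare the change at T3 with the change at T2. The word for values is also undefined and could mean monetary valuations rather than scale scores.

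Much of this stands. In particular, a reader might infer that the plan's adjustment runs backwards, discounting lasting benefit and leaving vanished benefit whole. The article does not support that as a finding: it does not say that the baseline-to-end difference is the rate deducted, and it does not rule out bringing in T2.

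The reply does not remove the narrower point. The sentence states prospectively how drop-off will be calculated, and it is the only such statement in the article. What it states does not match the definition in the methods section, so this is more than detail left to a fuller document. Sensitivity analysis varies a parameter; it does not correct one taken from the wrong contrast. The algebra holds for monetary valuations as well as for scores, provided they are obtained at the same times.

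**Conclusion.** The point holds in limited form. Followed as written, the stated calculation does not give the quantity it names, whether end of study means T3 (the natural reading) or T2. On the T3 reading it gives net benefit remaining and cannot distinguish no effect from an effect fully lost. Reversal of the adjustment is a conditional consequence, arising only if the difference itself is deducted.

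The size cannot be derived from the article. On the assumed 10-point gain, and on that conditional reading, the error ranges from none (half the gain lost) to the whole gain in either direction (fully sustained or fully lost), and is larger still if scores fall below baseline.

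The effect is confined to the SROI ratio. The models for DEMQOL, the Holden Communication Scale and the Approaches to Dementia Questionnaire are untouched.

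**What to change.** Replace the Discussion clause with a sentence such as: *Drop-off will be estimated, for each outcome valued, as the loss between T2 and T3 relative to the gain between T1 and T2, computed at group level and only where a T1–T2 gain is credited; its uncertainty will be varied in the SROI sensitivity analysis.* Add that decline from T2 to T3 may include disease progression as well as loss of benefit, since there is no randomised comparison to separate them.

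The cost is small: one sentence and a caveat, with no new visit, because the main questionnaires are already scheduled at all three times. An outcome without both an end-of-programme and a later value (observed well-being, for example, is last coded in the final two weeks of the programme) would need a stated range of assumed drop-off instead.

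The downside is that the ratio is imprecise when the gain is small. Group-level calculation and the restriction to credited gains limit this but do not remove it, so the range used in the sensitivity analysis should be reported with the SROI ratio.
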